### Interim analyses {21b}

No interim analyses were planned.

### Methods for additional analyses (e.g., subgroup analyses) {20b}

A secondary analysis of the primary endpoint will adjust for those pre-randomization variables which might reasonably be expected to be predictive of favorable outcomes (i.e., baseline LBM scores). Statistical inference will be based on one-sided *P* values and 95% confidence intervals which adjust for the stopping rule used for the primary analysis.

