### Trial design {8}

This study is a randomized, double-blind, placebo-controlled superiority trial. Patients will be randomized to either AmT-P or placebo supplementation upon admission to the treatment. Randomization is carried out at the hospital entry by adopting a stratification for the following parameters: (i) age (16–50); and (ii) body mass index (BMI) (BMI > 14 kg/m^2^). The treatment lasts 13 weeks.

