### Criteria for discontinuing or modifying allocated interventions {11b}

Patients may withdraw from the trial at any time for any reason. The AmT-P mixture was demonstrated as safe and tolerable at the same dosage and length in malnourished older adults [20]. We do not anticipate that severe harm to require early product discontinuation or medical intervention. However, participants will be withdrawn by the team involved in the trial if they experience any new-onset, moderate, or severe adverse events from the intervention. The trial will be terminated if > 20% of all participants exhibit adverse events of moderate or great severity which are new from baseline or progressively worsening.

No intervention dose modifications or administration frequency changes are allowed. Participants will be considered non-adherent and withdrawn from the trial if deviations from the dosing standard are reported to the study team.

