## Statistical methods

### Statistical methods for primary and secondary outcomes {20a}

At the end of the treatment, the LBM of the patient will be assessed, the blood chemistry and instrumental tests will be evaluated, and the scores of each questionnaire used will be calculated, assessing the effects of the treatment on the scores of each scale.

The univariate analysis (*t*-test for independent samples) will allow us to evaluate the differences at the end of treatment (T1) in the percentage of LBM between the intervention group and the control group. In addition, with mixed linear models, it will be possible to evaluate the difference between the two treatment arms in the primary and secondary outcomes at the end of therapy. Mixed linear models will be able to incorporate all available data collected in the study and effectively treat missing data commonly present in longitudinal studies. Models will be compared using maximum likelihood estimation rather than limited maximum likelihood estimation, as the focus is on the whole model, including fixed and random effects. The main clinical features (i.e., BMI, ED psychopathology, and general psychopathology) will be included in the models as potential predictors of the trajectories of change.

The analyses will also be controlled for physical activity and its variation between baseline and end of hospitalization (measured with the Actiheart system and IPAQ).

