### Composition of the data monitoring committee, its role and reporting structure {21a}

The data monitoring committee will be independent of the sponsor and will be composed of a medical doctor specialized in endocrinology, a medical doctor specialized in pharmacology, a psychologist, and a biostatistician. The data monitoring committee will review regular reports produced by the study team to ensure safe and responsible conduct of the trial and make any determination of discontinuation.

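### The inference rule for the additional analyses adjusts confidence intervals for a stopping rule that the plan does not have, and pairs one-sided P values of unstated level with 95% intervals

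*Protocol article*

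**What the plan says.** All references are to the protocol article.

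- **Methods for additional analyses {20b}** first announces a secondary analysis of the primary endpoint, adjusted for pre-randomization predictors such as baseline LBM. It then says: "Statistical inference will be based on one-sided *P* values and 95% confidence intervals". The intervals are further described as "95% confidence intervals which adjust for the stopping rule used for the primary analysis".
- **Interim analyses {21b}**, the section immediately before, says: "No interim analyses were planned".
- **Statistical methods for primary and secondary outcomes {20a}** describes an independent-samples t-test at T1 and mixed linear models for the end-of-therapy comparison. It gives no sequence of looks, boundary, sidedness or significance level.
- **Criteria for discontinuing or modifying allocated interventions {11b}** contains a termination criterion: "The trial will be terminated if > 20% of all participants exhibit adverse events of moderate or great severity".
- **Composition of the data monitoring committee {21a}** has the committee review regular reports to "ensure safe and responsible conduct of the trial and make any determination of discontinuation".
- **Trial design {8}** says: "This study is a randomized, double-blind, placebo-controlled superiority trial".

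**The concern.** Two things do not fit together.

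First, an interval adjusted for a stopping rule needs a rule under which the primary endpoint could have stopped the trial early: a schedule of looks and a boundary. The plan rules out interim analyses and describes none of this.

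Second, the sentence commits to one-sided P values without a level and sets them beside 95% intervals. The two lead to the same conclusion at one-sided 2.5% but not at one-sided 5%.

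What is at stake is the standard by which an analysis of the primary endpoint is judged. As written, an analyst must ignore part of the sentence and choose a level for the rest. If the choice were made after the data were seen, a borderline LBM difference could be reported either way. If the sentence applies only to the adjusted analysis, the same endpoint could also be judged by two different standards.

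**Working it through.** **1. Is there a stopping rule to adjust for?**

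| Provision | What triggers it | A look at LBM? |
|---|---|---|
| Interim analyses {21b} | none planned | no |
| Primary analysis {20a} | t-test at T1 and mixed models at end of therapy | no early look described |
| Termination criterion {11b} | share of participants with adverse events | no |
| Monitoring committee {21a} | regular reports on conduct and safety | no efficacy boundary given |

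None of these is a stopping rule of the primary analysis. The adverse-event criterion and the committee's remit supply no boundary on LBM from which an LBM interval could be adjusted.

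**2. Which test does the planned size fit?**

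Inputs from Sample size {14}: difference 10.8 − 8.8 = 2 percentage points, SD 3.2, 40 completers per arm. Level and power are not stated there, so conventional values are assumed.

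Normal approximation: n per arm = 2 × (z_α + z_β)² × (SD/difference)², with (3.2/2)² = 2.56.

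- Two-sided 5% (for a claim of benefit, the same as one-sided 2.5%), 80% power: 2 × (1.960 + 0.842)² × 2.56 ≈ 40.2, rounded up to 41. The t-based calculation gives 42. The stated 40 is reproduced to within one or two per arm.
- One-sided 5%, 80% power: 2 × (1.645 + 0.842)² × 2.56 ≈ 31.7, rounded up to 32 (t-based 33).
- One-sided 5%, 90% power: 44.

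The plan's 40 per arm therefore fits two-sided 5% or one-sided 2.5%, with no inflation for repeated looks. It does not fit one-sided 5% at either usual power.

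**3. Power at 40 per arm**

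SE of the unadjusted difference = 3.2 × √(2/40) = 0.716, and 2/0.716 ≈ 2.795.

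- One-sided 2.5% or two-sided 5%: Φ(2.795 − 1.960) = 79.8% (noncentral t 78.8%).
- One-sided 5%: Φ(2.795 − 1.645) = 87.5% (noncentral t 87.0%).

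**4. What the unstated level would change**

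Smallest observed difference that passes, with 78 degrees of freedom:

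- One-sided 5%: 1.665 × 0.716 = 1.19 points.
- One-sided 2.5% or two-sided 5%: 1.991 × 0.716 ≈ 1.42 points (1.424 before the inputs are rounded).

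| One-sided level (assumed) | False-benefit rate | Passes while the ordinary 95% interval includes zero |
|---|---|---|
| 2.5% | 2.5% | never |
| 5% | 5% | differences of about 1.19 to 1.42 points |

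These limits use the unadjusted SE. The analysis that precedes the disputed sentence adjusts for baseline LBM, and its SE, which the article does not give, may differ.

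**The case against.** The strongest reply has four parts.

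- **Harmless leftover.** With no interim look, an adjustment for stopping has nothing to act on and the interval reduces to the ordinary one. This stands: no estimate or interval need change. It does not remove the contradiction with the interim-analysis section, because the text still attributes a stopping rule to the primary analysis.
- **The level may sit elsewhere.** The article states no level, one-sided 2.5% is coherent with a 95% interval and fits the planned size, and an analysis plan may state it. This also stands. Silence on the level is not itself the fault. The fault is that the sentence fixes one-sidedness beside a 95% interval and does not say how the two relate.
- **Scope.** The sentence may apply only to the adjusted secondary analysis. That is possible, and the text does not settle it.
- **Safety stopping exists.** It does, but neither safety provision is part of the primary analysis.

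A reader might go further and infer that the trial's main test runs at one-sided 5% with a doubled false-positive rate. The document does not support this: it never states that level, and the sample size points away from it. A reader might also infer that harm could not be detected. That goes too far as well, since an ordinary two-sided 95% interval would show an LBM effect in the wrong direction, and adverse events are handled separately.

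**Conclusion.** The contradiction is established by the text alone: the intervals are to be adjusted for a primary-analysis stopping rule, and the plan has no interim analysis and no such rule. The sidedness statement is incomplete and its scope unclear.

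The numerical consequence is conditional. It is nil at one-sided 2.5%. At one-sided 5% it is a false-benefit rate of 5% instead of 2.5%, with the discordant band of about 1.19 to 1.42 points calculated above. That band assumes SD 3.2, 40 completers per arm and no covariate adjustment.

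This is a should-fix correction of the inference rule and does not show that the trial's error rate is inflated.

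**What to change.** Delete the stopping-rule clause and replace the sentence with one rule for primary and additional analyses, for example: *All tests are two-sided at the 5% level, with ordinary 95% confidence intervals; no interim analysis is planned and no adjustment for stopping is made.* For a claim of benefit this is equivalent to one-sided 2.5%, so stating that level explicitly would also be coherent. The two-sided form is simpler because it matches the interval directly and allows a difference in favour of placebo to be declared. The rule should be settled before unblinding.

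The cost is one sentence, with no new patients or data. Nominal power is lower than under a one-sided 5% test (about 79–80% against 87%), but it is the power that the planned size appears to have been chosen for.

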### Methods in analysis to handle protocol non-adherence and any statistical methods to handle missing data {20c}

We will test superiority using two analysis sets; the intention-to-treat set, considering all patients as randomized regardless of whether they received the randomized treatment, and the “per protocol” analysis set. Criteria for determining the “per protocol” group assignment will be established by Data Manager before the trial begins.

#### Imputation procedure for missing data

We will report reasons for withdrawal for each randomization group and compare the reasons qualitatively. Any missing data’s effect on results will be assessed via sensitivity analysis of augmented data sets. Dropouts will be included in the analysis by modern imputation methods for missing data.

The main feature of the approach is creating a set of clinically reasonable imputations for the respective outcome for each dropout. This will be accomplished using a set of repeated imputations created by predictive models based on the majority of participants with complete data. The imputation models will reflect uncertainty in the modeling process and inherent variability in patient outcomes, as reflected in the complete data.

After the imputations are completed, all of the data (complete and imputed) will be combined, and the analysis performed for each imputed-and-completed dataset. Rubin’s multiple (i.e., repeated) imputation method will be used to estimate the treatment effect. We propose to use 15 datasets (an odd number to allow use of one of the datasets to represent the median analytic result).

These methods are preferable to simple mean imputation, or simple “best–worst” or “worst-worst” imputation, because the categorization of patients into clinically meaningful subgroups, and the imputation of their missing data by appropriately different models, accords well with best clinical judgment concerning the likely outcomes of the dropouts, and therefore will enhance the trial’s results.

### Plans to give access to the full protocol, participant-level data, and statistical code {31c}

The datasets analyzed during the current study and statistical code will be available from the corresponding author on reasonable request, as be the full protocol.

## Oversight and monitoring

### Composition of the coordinating center and trial steering committee {5d}

The coordinating center is the Department of Eating and Weight Disorders of Villa Garda Hospital, Garda (VR), Italy. It will be responsible for running the trial day-to-day, including recruitment and data collection of all data, and management. [name] will provide supervision regarding the introduction and closing sessions. Clinical investigators, and study coordinators, will meet weekly.

### Composition of the data monitoring committee, its role and reporting structure {21a}

The data monitoring committee will be independent of the sponsor and will be composed of a medical doctor specialized in endocrinology, a medical doctor specialized in pharmacology, a psychologist, and a biostatistician. The data monitoring committee will review regular reports produced by the study team to ensure safe and responsible conduct of the trial and make any determination of discontinuation.

### Adverse event reporting and harms {22}

Adverse events will be formally assessed and graded according to severity at each biweekly medical visit via spontaneous reports of the participants. Adverse events reported by participants between study medical visits will be termed “spontaneous adverse events.” If an adverse event is of moderate or greater severity, the study team will coordinate with the patient’s physician and develop and document a response or monitoring plan.

The principal investigator ([name]) will evaluate the event’s causality to the trial intervention. Any event assessed as possibly, probably, or definitely related is classified as related to the trial intervention. The principal investigator ([name]) will make a severity assessment of the event as mild (i.e., a tolerable complication), moderate (i.e., it interferes with daily activities), or severe (i.e., it makes daily activities impossible). All serious adverse events will be documented and reported immediately (within a maximum of 24 h) to the principal investigator ([name]) and the health director of the Department of Eating and Weight Disorders of Villa Garda Hospital, Garda (VR). If it cannot be excluded that the severe adverse effect is attributable to the intervention under investigation, the principal investigator ([name]) will report it to the Ethics Committee of Verona and Rovigo, Italy, within 15 days.

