## Introduction

### Background and rationale {6a}

Anorexia nervosa (AN) is a severe eating disorder (ED) characterized by restriction of energy intake relative to requirement, leading to a significantly low weight, overvaluation of shape and weight, and persistent lack of recognition of the seriousness of the current low body weight. It has the highest mortality rate among all psychiatric diseases [1]. Multidisciplinary treatment incorporating medical, psychological, and nutritional interventions is the best practice for these patients [2, 3]. However, the underlying pathophysiology is unclear, and the outcome of recommended treatments is often unsatisfactory [4]. A recent systematic meta-review of meta-analyses and network meta-analyses has confirmed that no medication effectively reduces ED and general psychopathology and improves weight outcome in patients with AN [5]. These data support previous evidence that drugs cannot be recommended to improve body weight or specific psychopathology [4, 6] unless psychiatric comorbidity is present. On the other hand, weight restoration and the recovery of a normal nutritional status are key effective elements in the treatment of AN [7, 8], similarly to muscle and cognitive function improvement [9].

Assessment of nutritional aspects is crucial in the treatment of AN because evidence has shown that even beyond weight restoration, patients continue to show nutritional insufficiencies [10], a more limited spectrum of food preferences [11], and restricted dietary intake [12]. A recent systematic review and assessment of evidence quality on dietetic interventions for adult outpatients with an ED concluded that across the studies examining participants with AN, there was poor quality of evidence for the majority of outcomes measured (i.e., weight, ED behaviors, and psychopathology). They concluded that it is currently problematic for ED clinicians to draw firm conclusions about what should be enclosed in dietetic treatment for outpatients with AN [13].

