## Interventions

### Explanation for the choice of comparators {6b}

Participants will be randomized to the experimental formula AmT-P or placebo. An inert placebo is the correct comparator as the research serves to establish the safety and the efficacy is unknown. Future trials may include active comparators if collected data suggest clinical benefit. Placebo is an isocaloric product containing maltodextrins rather than AAs [22].

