#### Blood chemistry tests

They will include the following tests:Fasting blood glucose, triglyceridemia, HDL, total VLDL and LDL cholesterol, C reactive protein, fasting insulin, ALT, AST, ALP; GGT, GFR, NA, K, Ca, P, and Vitamin D-25OH.Metabolomic analysis (*n* = 15–20 patients/group) [45]. Plasma and urine samples will be collected at T0 and T1, immediately frozen on dry ice, and stored at − 80° C. The samples will then be manipulated for “targeted” metabolomic analysis (glycolysis, TCA cycle, amino acid metabolism) by high-resolution LC–MS liquid chromatography-mass spectrometry (LC–MS), in addition to the analysis of amino acid levels with Biochrom30^+^ (amino acid analyzer).miRNome analysis (*n* = 15–20 patients/group) [45]. Plasma and urine samples will be collected at T0 and T1, immediately frozen on dry ice, and stored at − 80 °C. The samples will then be manipulated to analyze miRNome (Next Generation Sequencing, NGS system).Mitochondrial mass and bioenergetics (*n* = 15–20 patients/group). Peripheral blood samples will be collected at T0 and T1. The circulating PBMCs will be isolated within 2 h of collection, pelleted, and immediately frozen on dry ice, then stored in biobank. Samples will be manipulated to analyze the following parameters: (i) mtDNA content, (ii) enzymatic functions of the respiratory chain complexes, (iii) production of ATP, (iv) transcriptome (RNA-seq method), and (v) methylome (whole-genome DNA methylation analysis) [20].Metagenomic analysis of the microbiota (n = 15-20 participants) [46, 47]. Stool samples will be collected at T0 and T1, immediately frozen in dry ice, and stored at − 80 °C. The samples will then be manipulated for metagenomics analysis.

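### Volunteered reports are the only stated route for finding non-serious adverse events, and no safety outcome is named although the placebo rationale says the trial is to establish safety

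*Protocol article*

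**What the plan says.** **Detection** (Protocol article, Adverse event reporting and harms {22}): this section opens by saying "Adverse events will be formally assessed and graded according to severity at each biweekly medical visit via spontaneous reports of the participants". The next sentence adds: "Adverse events reported by participants between study medical visits will be termed “spontaneous adverse events". Serious adverse events have their own route, with reporting within 24 hours, and that route is not limited to what participants report.

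**Grading** (same section): the lowest grade is "mild (i.e., a tolerable complication"; the other two are "moderate (i.e., it interferes with daily activities), or severe (i.e., it makes daily activities impossible". A moderate or worse event leads to a documented response or monitoring plan.

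**Rules that use the grades** (Criteria for discontinuing or modifying allocated interventions {11b}): a participant is withdrawn for moderate or severe events attributed to the product. The whole trial stops if more than 20% of participants have new or worsening events of at least moderate severity.

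**Purpose** (Explanation for the choice of comparators {6b}): "An inert placebo is the correct comparator as the research serves to establish the safety and the efficacy is unknown". Objectives {7} and Outcomes {12} list efficacy and mechanistic items only.

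**Laboratory data** (Blood chemistry tests): the panel includes "ALT, AST, ALP; GGT, GFR, NA, K, Ca, P, and Vitamin D-25OH". Statistical methods {20a} says blood chemistry is evaluated at the end of treatment. Research blood draws are stated for T0 and T1 (Blood samples).

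**The concern.** A formal assessment that records only what participants choose to mention is weaker than one in which everyone is asked the same thing. It tends to miss events, and what it finds depends on each participant's readiness to speak. Three things in this trial depend on the result: the comparison of harms between arms, the response plan, and the withdrawal and termination rules. If capture is incomplete, few recorded events may reflect the method of collection and not the product.

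The stated purpose adds to this. If establishing safety is part of the reason for using placebo, a reader expects a safety aim or outcome, and there is none. The protocol also collects liver, kidney and electrolyte values without saying how they relate to adverse events.

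**Working it through.** The point rests mainly on comparing passages. There is no stated figure to reproduce.

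1. **Detection.** The biweekly assessment works through spontaneous reports, and between-visit events are also participant-reported. No other route is stated for non-serious events. Keeping the label spontaneous for between-visit events would separate the two sources by method only if visit events were elicited, and the preceding sentence says they are not. The two sources still differ in timing.

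2. **Grading.** Mild is a tolerability grade. Moderate and severe refer only to daily activities. A raised liver enzyme or a low phosphate without symptoms does not interfere with daily activities, so it meets neither definition. It could still be recorded as mild, or reported as serious if it qualified.

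3. **What the grades feed.** Sections {11b} and {22} act on moderate or worse events. If all 92 randomised participants form the denominator, 0.20 × 92 = 18.4, so the termination rule needs at least 19 participants with a recorded qualifying event.

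4. **Effect of incomplete capture.** Let p be the true proportion of participants with a qualifying event and f the fraction captured.
   - The recorded proportion is f × p, so the rule is met only when p > 0.20 / f.
   - With equal f in both arms, the recorded risk difference is f × (p1 − p0), smaller than the true one when f < 1.
   - The recorded risk ratio is (f × p1) / (f × p0) = p1 / p0, which is unchanged.

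   The documents give no value for f. The direction follows from the algebra; the size does not.

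5. **Purpose against outcomes.** Section {6b} claims a safety purpose. Sections {7} and {12} contain no safety aim, adverse-event outcome or laboratory safety outcome. Aims and outcomes are core content of a protocol article, so condensation is an unlikely explanation.

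**The case against.** The strongest reply is that this is a condensed article of an efficacy trial. The fuller protocol may say how laboratory abnormalities become adverse events, and the assessment schedule (Table 3) is not reproduced. Participants are seen daily by nurses and biweekly by physicians, and an independent committee reviews regular reports. The safety phrase occurs once, in the comparator rationale, while section {11b} treats the product as already shown safe in malnourished older adults. Spontaneous may also be loose wording for anything a participant says at a visit.

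Much of this stands for the laboratory part: the article is silent, and silence is not exclusion. It does not answer the detection part, because section {22} states a method. The committee sees reports prepared by the study team, so it cannot restore what was never recorded. If visit events are in fact elicited, the sentence is wrong as written. The earlier safety study was in a different population and lasted 2 months, against 13 weeks here.

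A reader might infer more than the documents support:

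- **That abnormal laboratory results can never count.** Nothing excludes them, a mild grade is open to them, and serious events have a separate route.
- **That all grading is by daily activities.** Mild is not.
- **That the trial cannot inform on safety.** Double-blind, placebo-controlled event data have some value.
- **That these patients under-report because of** "persistent lack of recognition of the seriousness of the current low body weight". That phrase (Background {6a}) concerns low weight; nothing links it to reporting supplement side effects.
- **That the shortfall can be sized.** Setting f at 0.5 or 0.7 puts the true proportion needed for termination above 40% or 29% (0.20 / 0.5; 0.20 / 0.7), but both values of f are invented. The upper 95% bound of 6.3% for zero events in 46 (1 − 0.05^(1/46)) reflects the arm size and says nothing about detection.

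**Conclusion.** The concern holds in a limited form. For non-serious events the stated method is volunteered reporting, which tends to under-capture, and the arm comparison, response plan and rules in {11b} inherit that weakness. The safety purpose in {6b} has no counterpart in the objectives or outcomes. A symptomless laboratory abnormality has no stated route to moderate or severe.

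The size of the shortfall is unknown. The conclusion assumes that the text is followed as written and relies on the general tendency of volunteered reports to miss events; the documents do not measure that tendency. The laboratory part is the weakest, since a fuller protocol could resolve it. The primary efficacy analysis is not directly affected. The change is worth making because it is cheap and replaces a stated method with a better one.

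**What to change.** 1. At each biweekly visit already planned, have the physician ask every participant the same open question and a short fixed symptom list. Record separately what was volunteered between visits, and reword section {22} so that spontaneous refers to one source only.
2. Name adverse events and the T0–T1 changes in the blood chemistry already collected, by arm, as a safety outcome. Otherwise, reword section {6b} so that it does not claim to establish safety.
3. Reconcile in the text how blood chemistry results relate to the grades in {22} and the rules in {11b}. That is for the sponsor to settle, and no clinical threshold is proposed here. With the stated T0 and T1 draws, and chemistry evaluated at the end of treatment, these results would inform the arm comparison more than decisions during a participant's 13 weeks.

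**Cost:** a few minutes per visit and one results table, with no new samples or staff. More events will be recorded in both arms. Some may be moderate or worse and count towards the 20% termination threshold or lead to withdrawals, which would bear on the planned 80 completers. The sponsor should consider that before adopting the change.
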